#### Sample size

2.3.6

For this multicenter prospective cohort study, we calculated the sample size based on two primary outcomes: CRA recurrence and CRC occurrence. According to previous studies, the detection rate of CRA ranges from 15%-30% during 3-year follow-up and reaches 48%-68% during 5-year follow-up, while the annual incidence of CRC among adenoma patients is approximately 0.2%-0.5%.

We employed the cohort study sample size calculation formula N = (Zα/2 + Zβ)² × P(1-P)/d², where Zα/2 = 1.96 (α = 0.05, two-sided), Zβ = 1.28 (statistical power = 90%), and d represents the acceptable margin of error. Two primary outcomes guided our sample size determination: CRA recurrence and malignant transformation.

For the adenoma recurrence outcome, we considered the 5-year cumulative recurrence rate ranging from 48% to 68%, with a median of 58%. Using an absolute error of 2%, the minimum sample size calculation yielded 6,394 cases. After accounting for a 20% potential loss to follow-up, the adjusted sample size was 7,993 cases.

Regarding malignant transformation, the occurrence rate was estimated between 0.2% and 0.5%, with a median of 0.35%. We applied a relative error of 50% (0.175%), which resulted in a minimum sample size of 11,970 cases. Incorporating the 20% follow-up loss adjustment, the final target became 14,963 cases.

Considering the statistical requirements, research resources, and the need for robust analysis, we ultimately set the total enrollment target at 15,000 participants. This approach ensures adequate statistical power to detect clinically meaningful differences while providing comprehensive insights into CRA progression and cancer risk. This sample size ensures adequate statistical power to detect clinically meaningful differences in both primary outcomes while accounting for potential loss to follow-up. An interim analysis will be conducted when 50% of the target sample size is achieved.

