For continuous variables following normal distribution, independent sample t-tests will be used to compare differences between groups. For categorical variables, chi-square tests or Fisher’s exact tests will be applied as appropriate. Multivariate analysis will incorporate instrumental variables, multiple linear models, logistic regression (20), and Cox regression to explore the relationship between TCM syndromes and patient outcomes (21).

An interim analysis will be conducted when 50% of the target sample size is achieved. All statistical tests will be two-sided, with P<0.05 considered statistically significant.

Beyond determining the total sample size, we further considered the statistical power for key subgroup analyses. Based on prior literature reviews (22), the expected distribution of major TCM syndrome types in the study population is as follows: the “Dampness-Heat Accumulation” syndrome (dominant type) accounts for 28.70%, while the “Spleen Deficiency with Dampness Retention” and “Spleen Qi Deficiency” syndromes (major subgroups) account for 9.18% and 8.06%, respectively. With a total sample size of 15,000 participants, approximately 4,305 cases are expected to be classified under “Dampness-Heat Accumulation,” 1,377 under “Spleen Deficiency with Dampness Retention,” and 1,212 under “Spleen Qi Deficiency.” This sample allocation accurately matches the anticipated syndrome distribution, enabling the investigation of outcomes such as adenoma recurrence and malignant transformation, and fully meets the statistical requirements for comparative analyses among different TCM syndrome types.

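### The sample size is a one-proportion calculation, so it does not support the stated power to compare colorectal cancer occurrence between TCM syndromes

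*Protocol article*

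**What the plan says.** Section 2.3.6 of the protocol article gives the method: "We employed the cohort study sample size calculation formula N = (Zα/2 + Zβ)² × P(1-P)/d²". It sets "Zβ = 1.28 (statistical power = 90%), and d represents the acceptable margin of error". The inputs are 58% recurrence with an absolute error of 2 points, and 0.35% malignant transformation with a relative error of 50% (0.175 points). After a 20% allowance for loss, these give 7,993 and 14,963, and the target is set at 15,000. The section then concludes: "This sample size ensures adequate statistical power to detect clinically meaningful differences in both primary outcomes".

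Section 2.3.10 divides the full 15,000 by expected syndrome share: 28.70% for Dampness-Heat Accumulation ("approximately 4,305 cases are expected to be classified under" this type), 9.18% for Spleen Deficiency with Dampness Retention (1,377) and 8.06% for Spleen Qi Deficiency (1,212). It says that this allocation allows study of both recurrence and malignant transformation and "fully meets the statistical requirements for comparative analyses among different TCM syndrome types".

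The CRC rate is described in two ways. Section 2.3.6 introduces 0.2%-0.5% as an annual incidence, then enters its midpoint in the formula as the occurrence rate with no multiplier for follow-up time. The Introduction gives the same range as the share progressing to malignancy, with no time unit.

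**The concern.** The formula describes one overall proportion. With Zβ removed, it gives the number needed to estimate that proportion to within d. With Zβ kept, it can at most be read as the power of a one-sample test for a shift of d from a fixed rate. Neither version contains two groups, the share of patients in each, a hazard ratio or a number of events. The 90% therefore does not attach to any comparison between syndromes, and the group sizes in section 2.3.10 do not supply what is missing, because power for a rare outcome depends on events and not on heads.

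CRC occurrence is one of the two primary outcomes, and the link between TCM syndrome and prognosis is central to the study. If the power sentences stand, a null CRC-by-syndrome result could be taken as evidence of no difference from an adequately powered study, and an extreme estimate in a group with few events could be given too much weight.

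**Working it through.** **1. The plan's own figures.** With (1.96 + 1.28)² = 10.4976:

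- Recurrence: 10.4976 × 0.58 × 0.42 / 0.02² = 6,393.0, rounded up to 6,394; / 0.8 = 7,993. Both match.
- CRC: 10.4976 × 0.0035 × 0.9965 / 0.00175² = 11,956 (11,967 with unrounded Z values), against 11,970 stated; 11,970 / 0.8 = 14,963. This matches to within rounding.
- Without Zβ, a 95% margin-of-error calculation needs 2,340 and 4,376. The stated numbers are thus neither a plain precision calculation nor a two-group power calculation.

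**2. Expected CRC events.** Retained: 15,000 × 0.8 = 12,000.

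- Cumulative reading: 12,000 × 0.0035 = 42 (24 at 0.2%, 60 at 0.5%). By syndrome: about 12.1, 3.9 and 3.4.
- Annual reading: 5-year risk 1 − (1 − 0.0035)⁵ = 1.74%, about 209 events (119 to 297 over the range). By syndrome: about 60, 19 and 17.

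**3. CRC by syndrome, each named syndrome against all others.** For E events and syndrome share q, two-sided α = 0.05:

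- smallest HR at 90% power = exp(3.2415 / √(E·q(1−q)))
- power = Φ(ln HR × √(E·q(1−q)) − 1.96)

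Example: E = 42, q = 0.287 gives √(42 × 0.2046) = 2.93 and exp(3.2415 / 2.93) = 3.02.

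The protocol article states no effect size. The HRs of 1.5 and 2 below are assumptions.

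| | 28.70% | 9.18% | 8.06% |
|---|---|---|---|
| **Cumulative, 42 events** | | | |
| HR at 90% power | 3.0 | 5.7 | 6.3 |
| same, 24 to 60 events | 4.3 to 2.5 | 9.9 to 4.3 | 11.4 to 4.7 |
| Power at HR 1.5 | 22% | 12% | 11% |
| Power at HR 2 | 53% | 25% | 23% |
| **Annual, about 209 events** | | | |
| HR at 90% power | 1.6 | 2.2 | 2.3 |
| same, 119 to 297 events | 1.9 to 1.5 | 2.8 to 1.9 | 3.0 to 2.0 |
| Power at HR 1.5 | 75% | 39% | 36% |
| Power at HR 2 | 99.5% | 82% | 78% |

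The two smaller syndromes compared directly have about 7 events and 15% power at HR 2 on the cumulative reading, and about 36 events and 55% power on the annual reading.

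**4. Recurrence.** Retained in the two smaller syndromes: 12,000 × 0.0918 = 1,102 and 12,000 × 0.0806 = 967. Difference detectable with 90% power: 3.2415 × √(0.2436 × (1/1,102 + 1/967)) = 0.070, or 7 points. For an assumed 5-point difference against the rest, power is above 99%, 90% and 86% for the three syndromes.

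**5. Precision at 12,000 retained** (1.96 × √(P(1−P)/12,000)):

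- recurrence 58%: ±0.9 points
- CRC 0.35% (cumulative): ±0.11 points
- CRC 1.74% (annual over five years): ±0.23 points

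**6. Group count.** 0.0806 × 15,000 = 1,209, against 1,212 printed.

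**The case against.** The strongest objection is the rate. Section 2.3.6 itself calls 0.2%-0.5% annual. On that reading about 209 CRCs are expected, and power at HR 2 for each syndrome against the rest is 99.5%, 82% and 78%. A reader who sees the figure of 42 might infer that the study cannot compare CRC between syndromes at all. The documents do not support that: 42 follows from the way the formula uses 0.35%, but the text is ambiguous. Even on the annual reading, an HR of 1.5 is underpowered for all three syndromes, and the two smaller ones compared directly reach only about 55% at HR 2.

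Three further points stand in part:

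- Patients lost to follow-up contribute time to the planned Kaplan-Meier and Cox analyses, so 42 is conservative. The ceiling is 15,000 × 0.0035 = 52.5 if all losses came late, which is inside the 24 to 60 range already shown.
- The hazard ratios and the against-the-rest contrast are assumptions made here. The minimum detectable HRs need no assumed effect, only the contrast and 90% power.
- A reader might infer that the sample size is miscalculated or that recurrence is underpowered. Neither holds: the stated numbers reproduce, and recurrence has ample power.

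Detailed power tables may be left to an analysis plan. That does not cover the two sentences at issue, which assert power that the calculation shown does not provide.

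**Conclusion.** The concern holds as an unsupported power claim, with its practical effect confined to CRC by syndrome. The formula in section 2.3.6 cannot carry the statement about differences in both primary outcomes, and section 2.3.10 extends it to malignant transformation by syndrome with no calculation and no allowance for the 20% loss.

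The size of the shortfall depends on an unresolved input. If 0.35% is the risk over follow-up, only large hazard ratios are detectable. If it is annual, the design is reasonable for a hazard ratio near 2 for each syndrome against the rest, but not for smaller effects or for the two smaller groups against each other.

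These figures assume 12,000 retained, the plan's syndrome shares, proportional hazards and a two-sided 5% level. The annual reading also assumes a constant rate over a full five years. They ignore multiplicity, centre clustering and covariate adjustment, which would generally lower power. The 1,212 count is a minor slip without consequence.

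**What to change.** 1. In section 2.3.6, state whether 0.2%-0.5% is annual or cumulative over follow-up, and use it consistently there and in the Introduction. The remaining steps depend on this.
2. Describe the calculation as one of precision and give the 95% half-width at 12,000 retained: about ±0.9 points for recurrence, and for CRC about ±0.11 points if cumulative or ±0.23 if annual.
3. Replace the power sentences in sections 2.3.6 and 2.3.10 with minimum detectable hazard ratios by syndrome prevalence, computed from expected events after 20% loss and shown over the 0.2%-0.5% range.
4. If the cumulative reading is confirmed, state that CRC-by-syndrome comparisons are reported as estimates with intervals, and that a null result is not evidence of no difference. This step should not be taken if the rate proves to be annual.
5. Correct 1,212 to 1,209.

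The cost is rewording two paragraphs and adding a short table. The stated power for CRC becomes less favourable. No extra patients are needed.

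### The sample size is a one-proportion calculation, so the claimed power to detect between-group differences does not follow from it; for CRC that power depends on a time unit the plan leaves inconsistent.

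*Protocol article*

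**What the plan says.** Section 2.3.6 (Sample size) uses one formula for both primary outcomes, "N = (Zα/2 + Zβ)² × P(1-P)/d²", in which "d represents the acceptable margin of error". The z-values are for two-sided 5% and 90% power.

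- Recurrence: "we considered the 5-year cumulative recurrence rate ranging from 48% to 68%, with a median of 58" percent. "Using an absolute error of 2%, the minimum sample size calculation yielded 6,394 cases", or 7,993 after 20% loss.
- CRC: "the occurrence rate was estimated between 0.2% and 0.5%, with a median of 0.35" percent, with a relative error of 50% (0.175%). This gives 11,970, or 14,963 after 20% loss.

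The target is then set at 15,000. The section says twice that this gives adequate power for clinically meaningful differences, the second time as "This sample size ensures adequate statistical power to detect clinically meaningful differences in both primary outcomes".

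The time unit of the CRC range is not consistent. The first paragraph of section 2.3.6 calls 0.2%-0.5% an annual incidence. The calculation two paragraphs later uses it with no time unit, and the Abstract and Introduction also give none.

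Section 2.3.10 (Statistical analysis) expects three syndromes to make up 28.70%, 9.18% and 8.06% of participants. It says the resulting counts fully satisfy the needs of comparisons between syndromes, for outcomes that include malignant transformation. It gives no effect size, event count or power.

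**The concern.** The aims are comparative. The Introduction lists associations between exposures and recurrence or progression as a primary objective. Section 2.3.10 plans Cox models for risk factors and multivariable regression to "explore the relationship between TCM syndromes and patient outcomes". Power for such a contrast depends on the number of events, the share exposed and the effect sought. None of these enters the formula as a between-group quantity. At most, the Zβ term makes it a one-sample test of P against P ± d.

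What is at stake is how a CRC result will be read. If the protocol says power is assured, a non-significant association between a syndrome and CRC invites the conclusion that there is none. Whether the design could support that conclusion depends on an event count the plan leaves open by a factor of about five.

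**Working it through.** **1. The plan's own figures.** With "where Zα/2 = 1.96 (α = 0.05, two-sided), Zβ = 1.28 (statistical power = 90" percent), the multiplier is (1.96 + 1.28)² = 10.4976.

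- Recurrence: 10.4976 × 0.58 × 0.42 / 0.02² = 6,393.04, rounded up to 6,394; 6,394 / 0.8 = 7,992.5, so 7,993. Both match.
- CRC: 10.4976 × 0.0035 × 0.9965 / 0.00175² = 11,955 (11,966 with unrounded z), against 11,970 stated; 11,970 / 0.8 = 14,962.5, so 14,963. This agrees apart from a trivial difference.
- Without Zβ the formula would give about 2,340 and 4,375, so Zβ was included.

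The arithmetic is sound. What it delivers is information on two overall rates.

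**2. Events available for a comparison.** Evaluable: 15,000 × 0.8 = 12,000 (assumption: those lost contribute no events).

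- Recurrence: 12,000 × 0.58 = 6,960.
- CRC, 0.35% as 5-year cumulative risk: 12,000 × 0.0035 = 42 (24 at 0.2%, 60 at 0.5%).
- CRC, 0.35% per year for 5 years: 12,000 × [1 − (1 − 0.0035)⁵] = 208.5 (119.5 at 0.2%, 297 at 0.5%).

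**3. Detectable hazard ratio (Schoenfeld, two-sided 5%, 90% power).** HR = exp[(1.960 + 1.2816) / √(D × p × (1 − p))], where D is events and p the share with the syndrome, against all others. The plan names no contrast; this one is chosen to match its syndrome aims.

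Example: D = 42, p = 0.287. √(42 × 0.287 × 0.713) = 2.932; 3.2416 / 2.932 = 1.106; exp(1.106) = 3.02.

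| Outcome and reading | Events | p = 28.7% | p = 9.18% | p = 8.06% |
|---|---|---|---|---|
| Recurrence, 58% | 6,960 | 1.09 | 1.14 | 1.15 |
| CRC, 0.35% cumulative | 42 | 3.02 | 5.65 | 6.28 |
| CRC, 0.35% annual | 208.5 | 1.64 | 2.18 | 2.28 |

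Over 0.2%-0.5%, the 28.7% figure runs from 4.32 to 2.52 (cumulative) or from 1.93 to 1.52 (annual). With no loss at all, the cumulative case has 52.5 events and HR 2.69. For recurrence, the detectable absolute difference is about 3.2 points (28.7%) to 5.3 points (8.06%).

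**4. Power at fixed hazard ratios, p = 28.7%.** Power = Φ(ln HR × √(D × p × (1 − p)) − 1.96).

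- Cumulative, HR 2: Φ(0.693 × 2.932 − 1.96) = Φ(0.07) = 53%. At HR 1.5 it is 22%.
- Annual, HR 2: Φ(0.693 × 6.532 − 1.96) = Φ(2.57) = 99.5%. At HR 1.5 it is 75%.

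**5. Cross-check.** A two-proportion calculation gives detectable CRC risk ratios of 2.84, 3.73 and 3.91 (cumulative) and 1.60, 1.93 and 2.00 (annual) for the three syndromes. The methods agree well at 28.7%. They diverge for the small groups on the cumulative reading, where only about four and three cases are expected (12,000 × 0.0918 × 0.0035 = 3.9; 12,000 × 0.0806 × 0.0035 = 3.4). Either way the detectable effect there is large.

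**The case against.** The strongest reply concerns CRC. The only time unit the document attaches to 0.2%-0.5% is annual. Over 5 years that gives about 209 events, nearly full power for a doubling of hazard in the largest syndrome, and a detectable HR of 1.64. A reader might infer from the 0.35% calculation that the CRC power claim is simply false and that only a three-fold hazard is detectable. The documents do not support that as a fixed property of the design. It needs 0.35% to be a 5-year cumulative risk, about 12,000 followed, and the 28.7% contrast. The plan also names no clinically meaningful HR, so the supportable charge is that the claim is unsupported, not that it is disproved.

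The reply is also right on recurrence. A reader might infer that power is lacking for both outcomes, but any reasonable recurrence comparison has ample power.

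Nor is the possible misreading of a null CRC result something the plan itself commits to; it speaks of exploring relationships.

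What the reply does not rescue is the inference. The printed calculation is complete, and a between-group power claim cannot be drawn from it. This is a statement made in the article, not a detail left to a fuller document. Nor does the annual reading make power assured throughout: the two smaller syndromes still need an HR of about 2.2 to 2.3 on the Schoenfeld figures.

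**Conclusion.** The point holds as one about unsupported power statements. Section 2.3.6 sizes the study for two single proportions with a margin of error, and its two statements about power for differences do not follow. The claim in section 2.3.10 that syndrome counts suffice for comparisons, including of malignant transformation, is equally unsupported.

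For recurrence the practical consequence is small. For CRC the 90%-power HR for the largest syndrome is about 3.0 or about 1.6, depending on whether 0.35% is cumulative or annual. For the smaller syndromes it is about 5.7 to 6.3 or about 2.2 to 2.3. That a doubling would be missed about half the time holds only on the cumulative reading, for the 28.7% syndrome.

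These figures assume 20% loss with no events among those lost, one syndrome against all others, proportional hazards and no adjustment. Covariate adjustment, centre clustering and multiple syndrome comparisons would raise them.

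**What to change.** 1. State whether 0.2%-0.5% is an annual rate or a 5-year cumulative risk, and use it consistently in the Abstract, Introduction and section 2.3.6.
2. Limit the two power sentences in section 2.3.6 to what was calculated: precision of the overall recurrence and CRC rates.
3. Replace the between-group power claims in sections 2.3.6 and 2.3.10 with detectable HRs for each syndrome prevalence (28.7%, 9.18%, 8.06%) under the settled rate, with the range over 0.2%-0.5% and the assumed loss.
4. State that CRC contrasts will be reported with confidence intervals and that a non-significant CRC result will not be read as absence of association. Labelling every CRC comparison descriptive is not required; that would be a design preference, and hard to justify if about 209 events are expected.

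Cost: wording only. The stated power becomes less favourable; no extra patients are needed.

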#### Data collection

2.3.7

All data will be collected using a standardized electronic case report form (eCRF) through a dedicated multicenter research platform. The eCRF includes demographic information, medical history, colonoscopy findings, pathological results, and follow-up data. Research coordinators at each participating center will be responsible for timely data entry within 3 working days after each visit. The platform features built-in logical verification rules to ensure data completeness and accuracy during entry.

Source documents including colonoscopy reports, pathology reports, and laboratory results will be scanned and uploaded to the system. For privacy protection, all patient identifiers will be replaced with unique study codes, and access to the database will be restricted through a hierarchical authority management system. The database is equipped with automatic backup systems and advanced firewalls to prevent data loss and unauthorized access.

Missing data will be actively tracked and documented with specific reasons. For participants lost to follow-up, at least three telephone contact attempts will be made before declaring the loss. Multiple imputation methods will be applied for handling missing data during analysis, and sensitivity analyses will be conducted to assess the impact of missing data patterns.

#### Standardization of TCM assessments

2.3.8

##### Training and calibration of TCM assessors

2.3.8.1

TCM assessor training comprised two components: theoretical knowledge and operational procedures. For theoretical training, assessors were familiarized with the structure and individual items of the TCM syndrome differentiation questionnaire and TCM constitution scale in the case report forms. For operational training, assessors received standardized instruction on questionnaire completion methods, with all data entered via EDC systems.

##### Quality control procedures

2.3.8.2

A comprehensive quality control system was implemented under research monitor supervision. Monitors ensured complete and accurate completion of TCM syndrome questionnaires and constitution scales, checking for missing or erroneous entries.

Subject Selection: Subjects willing to participate in the survey were enrolled after receiving comprehensive explanation of the study significance and required information, ensuring informed consent was obtained.Researcher-administered Assessment: Trained researchers conducted item-by-item interviews with subjects and completed the questionnaires accordingly. All assessment sessions were audio-recorded for quality assurance purposes.

##### Centralized adjudication mechanism

2.3.8.3

A centralized adjudication system was established for both syndrome differentiation and constitution typing:

Syndrome Differentiation: Following the Guidelines for Integrated Traditional Chinese and Western Medicine Prevention and Treatment of Colorectal Adenoma, multiple licensed TCM practitioners received syndrome differentiation training. Syndrome determination was performed independently by pairs of practitioners in a blinded manner. Discrepancies were resolved through expert panel consensus. Inter-rater reliability for syndrome differentiation was assessed using Cohen’s kappa coefficient, with κ≥0.8 considered substantial agreement. Assessors achieving lower reliability underwent additional training until acceptable consistency was reached.Constitution Typing: Assessors performed individual constitution typing according to the Classification and Determination of TCM Constitution standards and training protocols.

